### Randomization

Randomization to treatment condition will be conducted using a computer-generated random digit procedure with two possibilities (B2S and TAU). Treatment outcome of school absence may be affected by the age of participants and the amount of school absence. Therefore, to ensure balanced groups, the randomization will be stratified on the presence of two factors, *age* (first to fourth grade [younger] or fifth to ninth grade [older]) and *amount of school absence* (< 50% [low] or > 50% absence [high]). To maintain similar treatment group sizes, the randomization will be conducted using permuted block randomization. The randomization is administered by staff outside the research group.

### Intervention

#### Back2School program

B2S is a manualized CBT program developed for this study, aimed at treating youths with SA. The B2S program is used together with the transdiagnostic MMM manual [23]. The MMM manual comprises evidence-based CBT methods and techniques organized into disorder-specific modules to target subclinical or clinical levels of anxiety, depression, behavioral disturbance, and trauma-related problems. The CBT methods and techniques in the MMM manual are adapted from EBT programs targeting each of the specific domains of problems in children and adolescents. The MMM manual supplements the B2S program, and the B2S manual refers to relevant material from the MMM manual.

The B2S manual is specifically developed for treating SA. Intervention is determined via a descriptive functional analysis obtained via the School Refusal Assessment Scale (SRAS) [24] together with a case formulation approach to planning CBT for attendance problems. The functional approach involves identifying the motivational function of the child’s SA. Motivational functions include (1) avoidance of school-based situations that provoke negative affectivity, (2) avoidance of aversive school-based social/evaluative situations, (3) pursuit of attention from significant others outside of school, and (4) pursuit of tangible reinforcement outside of school [24–26]. The first two motivational functions refer to negative reinforcement; the latter two motivational functions refer to positive reinforcement. SA motivated by positive reinforcement suggests CBT procedures such as parent management, contingency management, and contracting to minimize incentives for SA and boost incentives for attendance. SA motivated by negative reinforcement suggests CBT procedures such as cognitive restructuring and exposure-based practice to reduce the anxious or depressive physical sensations and thoughts. In the development of the intervention, we adapted aspects of the @SCHOOL intervention [27] and the When Children Refuse School intervention [25, 28].

The intervention consists of a 1.5-h clinical interview with the youth and parents aimed at designing a case formulation and a treatment plan and preparing the family for the first therapy session, ten 1-h sessions with the child and parents together (except for sessions 2 and 6, which are only with the parents), a 1-h booster session with the child and parents together, and four school meetings. With the aim of instilling hope for change in the family, to speed up the change process, and to show the family that the SAP is taken seriously, the first 2 weeks of the intervention involve two sessions per week. For the following six sessions, there is the option to schedule them weekly or once every 2 weeks as decided to be appropriate by the therapist and the family together. The implementation of the booster session is flexible regarding the timing and will be held within 1–3 months after the last session. An important part of the B2S intervention is to collaborate with the school. In addition to the sessions with the child and parents, four meetings with participation of teachers from the youth’s school, the therapists, and the parents are conducted. The meetings will take place at the child’s school at the beginning, the middle, and the end of the treatment period, as well as shortly after the booster session. For a detailed overview of the intervention, *see* Table 1.

**Table 1 Tab1:** Overview of the Back2School program

Session number	Duration (h)	Participants	Session content
S-0	1.5	T, C, P	Structured assessment interview with the family conducted by the therapists (a clinical psychologist and a clinical psychology graduate student). The family receive handouts regarding psychoeducation and SMART goals as homework for session 1.
Clinical conference	1	T	The therapists are discussing the case formulation, choice of treatment modules, and treatment goals with a clinical psychologist at CEBU
S-1	1	T, C, P	Presenting and discussing the case-formulation with the family. Psychoeducation regarding school absence, and development of SMART goals.
S-2	1	T, P	Parent only session 1. Helping the parents to clarify and solve potential questions/problems regarding school placement, somatic symptoms in child, and parental motivation for change. Planning better routines at home. Working with potential sleep problems.
S-3	1	T, C, P	Planning the date for returning to school, and planning the first day back in school. Creating a gradual exposure plan for returning to school.
S-4	1	T, C, P	Psychoeducation regarding the youth’s primary problem related to school absence (anxiety, depression, or behavioral problems) by including the MMM Modules. Continuing work with the gradual exposure plan for returning to school.
S-5	1	T, C, P	Continuing work with CBT methods regarding the youth’s primary problem related to school absence (e.g. exposure, behavioral activation and/or cognitive restructuring) by including the MMM Modules. Continuing work with the gradual exposure plan for returning to school. Working with boundaries.
S-6	1	T, P	Parent only session 2. Working with parent behavior. Identifying and reducing factors at home that maintain school absence.
S-7	1	T, C, P	Continuing to work towards returning to school. Revising gradual exposure plan. Focusing on how parents can support the youth in exposure exercises, and returning to school. Problem solving
S-8	1	T, C, P	Open session tailored to needs of the youth and parents. Continue working with CBT methods by including the MMM Modules. Open session tailored to needs of the youth and parents. Continue working with CBT methods by including the MMM Modules.
S-9	1	T, C, P	
S-10	1	T, C, P	Concluding the program. Focusing on maintaining and continuing the progress.
Booster	1	T, C,P	Focusing on maintaining and continuing the progress. Problem solving regarding relevant problems. Advise possible further help.
SM 1	1	T, P, S	Presenting and discussing the case formulation with the school. Planning the schools role in the youth’s return to school. Informing the school about the B2S and CBT approach.
SM 2	1	T, S	Following up on the youth’s progress in the school setting. Discussing potential academic difficulties, problems regarding bullying or other problems.
SM 3	1	T, S	Planning how the school can continue to help and support the youth. Discussing relapse prevention.
SM 4	1	T, S	Planning how the school can continue to help and support the youth. Discussing relapse prevention.

*Abbreviations: B2S* Back2School, *C* Child, *CBT* Cognitive behavioral therapy, *MMM* Mind My Mind, *P* Parent, *S* School officials, *S* Session, *SM* School meeting, *SMART* Specific, measurable, attainable, realistic, time-bound, *T* Therapist

#### Clinical interview and case formulation

Initially, the families in the B2S group attend a 1.5-h structured clinical interview held by the appointed therapists. The interview is designed to get an understanding of the youth’s SA, development, family and social situation, and functioning in daily life. The interview also includes a brief, semistructured psychopathological interview developed for the study with the child and parents together. Based on the qualitative and quantitative information derived from the interview and the preintervention assessment battery, a case formulation is developed by the therapists. At a clinical case conference, the case formulation is discussed with a clinical psychologist at CEBU, and a preliminary treatment plan is constructed.

#### Therapists

School psychologists from Aarhus Municipality and clinical psychologists from CEBU will conduct the B2S intervention together with a clinical psychology graduate student at CEBU as cotherapist. There is one psychologist and one cotherapist per case. All therapists and cotherapists receive a 6-day training course and four 1-day brush-up courses regarding assessment, case formulation, and the B2S and MMM manuals. In total, therapists and cotherapists receive 80 h of training. All therapists and cotherapists receive weekly face-to-face group case supervision by specialists in clinical child psychology.

### Treatment as usual

The help that the municipality provides to youths with SA varies and is dependent on the available resources in the school and the municipality, as well as the youths’ presenting problems. The TAU intervention is requested by the schools and is usually provided by Aarhus Municipality’s school psychologists, but it could also consist of counseling by teachers or social workers. For example, the interventions could be meetings with the school and/or the families, individual counseling with the child, flexible school hours, or transfer to special education classes (Aarhus Municipality, 2013). To keep track of the different interventions in the TAU condition, a telephone interview will be conducted with the parents in the TAU group at T2, investigating which interventions participants in the TAU condition have received.

### Outcomes

An overview of the included outcome measures and raters (child, parents, and teacher) is presented in Table 2.

**Table 2 Tab2:** Overview of outcome measures, respondents, and assessment points

Measures	Respondent	Time							
		T1		T2		T3		T4	
		B2S	TAU	B2S	TAU	B2S	TAU	B2S	TAU
Primary outcome measure									
School absence: registry	M	●	●	●	●	●	●	●	●
School absence: parent-reported	P	●	●	●	●	●	●	●	●
Secondary outcome measures									
SDQ	Y, P, T	●	●	●	●	●	●	●	●
PECK	Y	●	●	●		●		●	
FAD	Y, P	●	●	●		●		●	
SCAS	Y, P	●	●	●		●		●	
MFQ	Y, P	●	●	●		●		●	
CHU-9D	Y	●	●	●	●	●	●	●	●
SEQ-SS	Y	●	●	●	●	●	●	●	●
SEQ-RSAP	P	●	●	●	●	●	●	●	●
Other measures:									
Background information	P, T	●	●	●	●	●	●	●	●
School and family collaboration	P, T	●	●	●	●	●	●	●	●
ESQ	Y, P, T			●	●				
SRAS-R	Y, P	●	●						

*Abbreviations: B2S* Back2School, *CHU-9D* Child Health Utility 9D Index, *ESQ* Experience of Service Questionnaire, *FAD* Family Assessment Device, *M* Aarhus Municipality, *MFQ* Mood and Feelings Questionnaire, *PECK* Personal Experience Checklist, *P* Parent, *SCAS* Spence Children’s Anxiety Scale, *SDQ* Strength and Difficulties Questionnaire, *SEQ-RSAP* Self-Efficacy Questionnaire for Responding to School Attendance Problems, *SEQ-SS* Self-Efficacy Questionnaire for School Situations, *SRAS-R* School Refusal Assessment Scale–Revised, *T* Teacher, *Y* Youth

#### Primary outcome

The primary outcome is school attendance, which is measured in two ways:It is mandatory for all public schools in Denmark to report school absence data for all schoolchildren on a daily basis. Daily school absence data for youth included in the study will be provided by Aarhus Municipality. Absence data 1 year prior to the youths’ inclusion in the project and at follow-up are also provided by the municipality.Retrospective daily school absence for a 2-week period (10 schooldays) is reported by parents at all assessment points (as part as the assessment battery at preassessment, postassessment, and follow-up).

In addition, the families in the B2S group will register daily absence for each lesson throughout their course in the B2S intervention.

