**Methods/design:**

One hundred sixty children, aged 7 to 16 years, will be randomly assigned to either Back2School or TAU. The design is a two (Back2School and TAU) by four (preassessment [T1], postassessment [T2], and 3-month [T3] and 1-year [T4] assessments) mixed between-within design. The primary outcome is school attendance based on daily registration. Secondary outcomes pertain to youth psychosocial functioning, quality of life, bullying, self-efficacy, and teacher-parent collaboration. These secondary outcomes are measured via youth, parent, and teacher reports.

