Some children with problematic SA display anxiety and/or depression; some display externalizing problems, some display both, and some display other problems, (e.g., at a family or school level). In addition, negative cognitions concerning the ability to cope with situations associated with school attendance have been shown to be prevalent among children with problematic SA [18, 19]. Self-efficacy concerning school situations has been found to increase following treatment, and treatment that increases self-efficacy may reduce anxiety, depression, and behavior problems and facilitate reengagement with schooling [20].

An intervention that addressed the needs of this very heterogeneous group therefore needs to be based on an initial assessment and case formulation, followed by a modular, transdiagnostic approach that includes evidence-based interventions for anxiety, depression, behavior problems, parent training and teacher training, and a focus on increasing self-efficacy.

The main objective of this study is to test the efficacy of Back2School (B2S) [21], a modular transdiagnostic CBT intervention aimed at increasing school attendance and decreasing anxiety, depression, and behavior problems among youth with problematic SA. The study uses an RCT design with an active control group receiving treatment as usual (TAU). Based on previous studies, our primary hypothesis is that the B2S intervention will be superior to TAU in improving school attendance. Secondary hypotheses are that the B2S intervention will be superior to TAU in reducing anxiety, depression, and behavior problems. We further hypothesize that improvement in school attendance will be mediated by reductions in the youths’ anxiety, depression, and behavior problems and increases in the youths’ and parents’ self-efficacy. Other members of our research team will perform an economic evaluation comparing the B2S group with the TAU group, both in terms of cost utility measured with a quality-of-life measure and in terms of cost benefit measured by subsequent obtained grades, youth education, employment, and income.

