### Sample size

On the basis of findings of recent meta-analyses of both truant SA [10] and SR SA [11], we expect to find a standardized effect size regarding SA in the range of 0.46–0.54. The targeted sample size is 70 per condition to provide sufficient statistical power (0.80) and a significance level (0.05, two-tailed) to find a generalized effect size regarding SA of 0.54. Similar RCTs have a mean attrition rate of 10% [44–47]; therefore, 80 participants are included in each condition (B2S *n* = 80, TAU *n* = 80).

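### The primary outcome is one measure in the abstract (daily registration) and two unranked measures in the body (registry and parent recall), while the sample size assumes a single effect

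*Protocol article*

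**What the plan says.** All references are to the protocol article.

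- **Abstract, Methods/design.** One measure: "The primary outcome is school attendance based on daily registration".
- **Primary outcome.** Two measures: "The primary outcome is school attendance, which is measured in two ways". The first is the municipal registry: "Daily school absence data for youth included in the study will be provided by Aarhus Municipality". The second is parent recall: "Retrospective daily school absence for a 2-week period (10 schooldays) is reported by parents at all assessment points". The recall item is part of the assessment battery.
- **Outcomes, Table 2.** Under the primary heading stand a registry row and a row labelled "School absence: parent-reported". Both are marked for both arms at T1 to T4, with no ranking.
- **Background.** The hypothesis names no measure: "our primary hypothesis is that the B2S intervention will be superior to TAU in improving school attendance".
- **Sample size.** 70 per arm for 0.80 power at two-tailed 0.05 to detect one standardized effect on absence of 0.54, raised to 80 per arm for 10% attrition.
- **Primary study parameters.** The same mixed model is applied to every repeatedly measured outcome, without singling out a primary one.

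Three further statements bear on the choice between the measures. The section on participants and eligibility excludes pupils for whom the municipality cannot supply absence data, and it expects more attrition in TAU on the secondary measures. The Back2School program section has parents attending the sessions. The Primary outcome section adds a record kept in one arm only: "the families in the B2S group will register daily absence for each lesson throughout their course in the B2S intervention".

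**The concern.** A protocol has to identify the outcome that decides the trial. This one identifies it in two ways that cannot both be right. The two measures are not interchangeable: one is mandatory daily registration by the school, the other a parent's recall of 10 schooldays. They could give different answers, and the text as it stands would let either be presented as the primary result.

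Two things are at stake. The first is the error rate: a single 5% test was planned for, and a choice between two results is not a single test. The second is bias. Parents in B2S take part in the treatment and so know their allocation. Their report is collected by questionnaire, where loss may differ by arm. Neither problem applies to the registry in the same way.

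**Working it through.** **1. The plan's own figure.** Inputs from Sample size: d = 0.54, two-sided alpha 0.05, power 0.80.

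n per arm = 2 × (1.960 + 0.842)² / 0.54² = 2 × 7.85 / 0.2916 ≈ 53.8, so 54 (55 with the t distribution).

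The stated 70 is larger. With 70 per arm, power at d = 0.54 is about 0.89. The attrition step is 70 / 0.9 = 77.8, so 78, which is consistent with 80. That 70 does not reproduce is a separate matter. What counts here is that the calculation is for one effect and one test.

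**2. Error rate under each possible decision rule.** Let Z1 and Z2 be the two test statistics, with correlation r under the null. The documents give no r, so the range below is an assumption.

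- Either measure suffices: 1 − P(|Z1| ≤ 1.96 and |Z2| ≤ 1.96). At r = 0 this is 1 − 0.95² = 0.0975.
- Either suffices, counting only results in favour of B2S: 1 − P(Z1 ≤ 1.96 and Z2 ≤ 1.96). At r = 0 this is 1 − 0.975² = 0.0494, against 0.025 for one test.
- Both must be significant, no effect on either: P(|Z1| > 1.96 and |Z2| > 1.96). At r = 0 this is 0.05² = 0.0025.

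| Assumed r | Either, two-sided | Either, favouring B2S | Both significant |
|---|---|---|---|
| 0 | 9.75% | 4.9% | 0.25% |
| 0.3 | 9.5% | 4.8% | 0.5% |
| 0.5 | 9.1% | 4.5% | 0.9% |
| 0.7 | 8.3% | 4.2% | 1.7% |
| 0.9 | 7.0% | 3.5% | 3.0% |

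If both must succeed and only one measure truly has an effect, the error is limited by the 5% test on the other. If the registry alone decides, it is 5%.

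**3. Cost of keeping two primary measures.** With alpha 0.025 each and 70 per arm, power (t-test) is 0.82 at d = 0.54 and 0.68 at d = 0.46, the lower end of the range the protocol expects. With one measure at 0.05 the corresponding figures are 0.89 and 0.77.

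**4. Exposure of the parent report to bias.**

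- *Knowledge of allocation.* Blinding is not mentioned. For B2S it follows from the session schedule that parents know their arm.
- *Loss.* The protocol ties its expectation of larger TAU attrition to the secondary measures. The parent report travels in the same battery, so the same loss is likely. This is an inference.
- *Diary.* The B2S lesson-by-lesson record runs only during treatment. It cannot affect T1, and the T3 and T4 recall windows would normally fall after treatment. It may affect recall near T2. Nothing in the document shows that it does, or in which direction.

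**The case against.** The strongest reply has four parts.

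*The document already leans to the registry.* The abstract names it, Table 2 lists it first, and eligibility is built around the availability of municipal absence data. This stands. It makes the registry the likely intention and supports the fix. It does not remove the conflicting text in the Primary outcome section and Table 2.

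*Decision rules and sharing of alpha belong in an analysis plan, which is not shown.* This also stands, and the absence of such a rule is not the point made here. The point is that the protocol article contradicts itself on what the primary outcome is.

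*The error rate is not shown to be wrong.* A reader might infer that both measures are each tested at 5% and that the primary error rate is therefore not 5%. The document says neither. Its only 0.05 is in the sample-size paragraph, for one effect, and no section says that a win on either measure counts. The error rate is left open by the text.

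*The inflation figures look larger than the risk of a false claim of benefit.* They count rejections in both directions. A false claim favouring B2S is at most 5% under an either-wins rule, against 2.5% for one test. Both measures record the same children's absence, so a high correlation and a smaller inflation are plausible. This is correct and is shown in the table.

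On attrition, the protocol also plans mitigation: a shorter battery for TAU and a gift card after each later assessment. These may reduce differential loss, but the registry does not depend on questionnaires being returned at all.

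**Conclusion.** The inconsistency is real and should be resolved: one primary measure in the abstract, two unranked ones in the Primary outcome section and Table 2, and a sample size for one effect at two-sided 0.05.

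Its size depends on a rule the document does not state. Under an either-wins rule at 5% each, the two-sided familywise error is about 7.0% to 9.5% for assumed correlations of 0.9 to 0.3, and 9.75% at zero. The chance of a false claim favouring B2S is then 3.5% to 4.9% over correlations of 0.9 to 0, against 2.5%. If the registry alone decides, or both must succeed, the two-sided error stays at or below 5%. It would go too far to say that the error rate is wrong, or that the trial could give no answer if the measures disagreed.

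The risks of bias in the parent report are reasoned from the design. Knowledge of allocation in B2S is secure, greater TAU loss is likely, and an effect of the diary on recall near T2 is only possible. Together they are good grounds for not letting that measure carry the confirmatory claim.

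**What to change.** Before any outcome data are analysed by arm:

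1. Name school attendance from the municipal registry as the sole primary outcome, tested at two-sided 5%, as in the abstract.
2. Make the parents' 10-schoolday report a secondary or supportive outcome, and report its missingness by arm.
3. Align the Primary outcome section and Table 2 with this.

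The cost is wording in two places. N is unchanged and the registry outcome loses no power. Keeping both as primary with alpha split would instead cost the power shown in step 3 of the working. Timing matters, because a choice made after the results by arm are known would weaken the confirmatory claim.

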#### Secondary outcomes

##### Strength and Difficulties Questionnaire

The Strength and Difficulties Questionnaire (SDQ) [29] will be used to measure emotional, behavioral, and social difficulties. The SDQ consists of a self-report version (from age 11) and two proxy report versions for parents and teachers. All three informants complete the SDQ. The SDQ is a brief behavioral screening questionnaire and consists of 25 items rated on a 3-point scale. The items are divided into five 5-item subscales that generate a score for emotional symptoms, conduct problems, hyperactivity/inattention, peer relationship problems, and prosocial behavior. The total difficulties scale sums up the difficulties across the four problem areas (not including lack of prosocial behavior). The extended version of the SDQ also asks questions about child distress and interference of problems with home life, friendships, classroom learning, and leisure activities, each scored on a 4-point scale. The impact scale sums up the distress and interference of problems, counting only the moderate and severe levels. The SDQ is a well-established and widely used measure that has shown good psychometric properties in a Danish population [30].

